### Endpoint criteria

Patients finish 5-year idebenone treatment;Patients develop overt α-synucleinopathies according to the diagnostic criteria. The definition of α-synucleinopathies in the endpoint contains three most common types: PD, DLB and MSA.

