### Discontinue/withdraw criteria of patients

Pregnant;Poor compliance to the protocol;Serious complications or other severe diseases happen during the administration and the continuation shows little benefits;Significant disease progression and the discontinuation is necessary after evaluation;Meet the exclusion criteria (newly or already confirmed);Unable to receive the intervention as scheduled.

Participants will be included in the final statistical analysis if they accomplish three courses of treatment and evaluation, otherwise will be excluded.

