
### Outcome measures

The primary outcome is the comparison of conversion rate from iRBD to synucleinopathies between idebenone and placebo group, measured at 5-year of follow-up. Clinical symptoms will be evaluated by physicians using comprehensive rating scales. PET/MRI will be carried out to reflect the dopaminergic degeneration. The secondary outcome is the safety and tolerability of idebenone in the treatment of patients with iRBD. The objects for safety evaluation should contain all the participants that have been administrated with the experimental drug. Safety evaluation including the laboratory test results, the events of death and adverse reactions, will be recorded in detail and analyzed after the trial (Table 1).

**Table 1 T1:** Outcome measures taken at baseline and follow-up.

**Endpoint**		**Measure**	**Evaluating methods/criterion**	**Time points**
Primary	Effectiveness: 5-year conversion rate of iRBD into synucleinopathies	Rating scales	MDS-UPDRS, RBDSQ, MMSE, MoCA, SS-16, HAMD-17, NMSQ, SCOPA-AUT	Baseline, 1, 3, 5 years
		Blood testing	Biomarkers including neuronal exosomal α-synuclein, SNCA methylation, inflammatory cytokines and chemokines (IL-8, TNF-α, TGF-β, IL-10, IL-6, CXCL12, CX3CL1, CCL15, CCL3 and CCL20)	
		Neuroimaging examinations	(^18^F-FP-CIT) DAT-PET/ MRI	
Secondary	Safety and tolerability	Vital signs	Body temperature > 39.5°C, pulse rate <50 beats/min, blood pressure < 80/60 mmHg, blood pressure > 220/120 mmHg, oxygen saturation < 90%;	Every 6 months
		Electrocardiogram	Atrial fibrillation, complete atrioventricular block, sinus arrest, ventricular tachycardia, ventricular fibrillation, pathologic Q-waves, arched ST-segment elevation	
		Laboratory tests	The ratio of alanine aminotransferase to aspartate aminotransferase over twice the normal values after treatment, the creatinine over twice the normal value, glomerular filtration rate lower than 20 ml/min, red blood cell, hemoglobin, white blood cell and platelet count <50% of the lower normal limit or more than twice the upper normal limit	
		Adverse events	Result in death, are immediately life-threatening or cause severe organ damage	

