### Sample size and statistical analysis

The 5-year conversion rate of participants treated with idebenone is expected to decrease from 47% in the placebo group to 25%. The idebenone and placebo group are randomized at a ratio of 1:1, and a 5% drop-out rate is considered throughout the study. We estimated that 71 patients would be needed in each treatment group to allow for a power of 80% at two-sided α-level of 5%. In total, 142 patients are projected to be enrolled.

Statistical analysis will be performed using SPSS 27.0, STATA 17.0 and GraphPad Prism 9.4.0. Data will be analyzed on an intention-to-treat basis using two-sided tests with *p* < 0.05 considered significant. Continuous variables will undergo normality test as well as ANOVA test for inter-group comparison. Categorical variables will be compared using Chi-square test, Fisher's exact test or Wilcoxon rank-sum test. To assess the five-year conversion rate from iRBD diagnosis to clinically diagnosed synucleinopathies between patients treated with idebenone and placebo, we estimated the hazard ratio (HR) using a Cox proportional hazards model. Kaplan-Meier method will be applied to estimate median progression-free survival (PFS) and corresponding 95% confidence interval (CI) and survival curves will be plotted.

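### The rule admitting only patients who complete three courses to the final analysis contradicts intention-to-treat, and could drop many converters if conversion ends participation

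*Protocol article*

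**What the plan says.** Two sections of the protocol article define who is analysed.

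- *Discontinue/withdraw criteria of patients*, closing sentence: "Participants will be included in the final statistical analysis if they accomplish three courses of treatment and evaluation, otherwise will be excluded". It carries no per-protocol or sensitivity label and refers to the final analysis as a whole.
- *Sample size and statistical analysis*: "Data will be analyzed on an intention-to-treat basis using two-sided tests". The same section plans a Cox model for the comparison of conversion, with Kaplan-Meier curves.

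Three other places bear on what the completer rule would do.

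- *Endpoint criteria* lists two items: finishing the 5 years of treatment, and "Patients develop overt α-synucleinopathies according to the diagnostic criteria". It does not say whether treatment or visits stop at conversion.
- The withdrawal list includes disease progression where stopping is judged necessary, and newly meeting an exclusion criterion. *Exclusion criteria* names bradykinesia, tremor and postural instability.
- *Study designs* and Table 1 set follow-up evaluations at years 1, 3 and 5. The term *course* is not defined anywhere.

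**The concern.** An intention-to-treat analysis keeps every randomised patient in the assigned arm. A rule that admits only completers conditions on what happens after randomisation. The reasons for not completing listed in the same section (progression, serious complications, poor compliance, inability to take the treatment) are plausibly related to treatment, to outcome or to both. Patients who die or are lost go the same way. The groups left are no longer those that randomisation formed.

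The exclusion also serves no purpose in the planned analysis. Cox and Kaplan-Meier methods take each patient's time to conversion or to last assessment, so incomplete follow-up is handled by censoring.

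The further risk is to the primary events. If a patient who converts early leaves the trial, that patient does not reach the third evaluation and would be removed from the analysis because the primary event occurred. In that case the 5-year conversion rates would be understated and most of the planned power could be lost.

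**Working it through.** **Inputs from the protocol article (*Sample size and statistical analysis*).** 5-year conversion 47% on placebo and 25% on idebenone, 1:1 allocation, 71 per arm, two-sided 5%, power 80%, 5% drop-out.

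**The plan's own figure.** Two proportions with unpooled variance: n = (1.960 + 0.842)² × (0.47×0.53 + 0.25×0.75) / 0.22² = 7.849 × 0.4366 / 0.0484 = 70.8, so 71 per arm. This matches the stated number before any drop-out allowance. With 5% drop-out the same formula gives 70.8/0.95 = 74.5, so 75. That shortfall is a separate matter and does not affect this point.

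**Events if everyone is analysed.** 71×0.47 = 33.4 and 71×0.25 = 17.8, together 51.1.

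**Assumptions needed to size the completer rule.** (i) The three courses are the evaluations at years 1, 3 and 5, the only set of three in the document. (ii) Converters found by the year 3 visit leave, and conversions between years 3 and 5 are counted at year 5. (iii) Timing within 5 years follows F(t) = 1 − (1−p)^((t/5)^k), where k = 1 is a constant hazard. The document gives only 5-year rates, so k is assumed. No other drop-out is applied.

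**Constant hazard (k = 1).**

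| | Placebo | Idebenone |
|---|---|---|
| Converted by year 3, F(3) | 0.317 | 0.159 |
| Share of converters dropped, F(3)/p | 67% | 63% |
| Patients left, 71×(1−F(3)) | 48.5 | 59.7 |
| Events left, 71×(p−F(3)) | 10.9 | 6.5 |
| Analysed rate | 22.4% | 10.9% |

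Events left: 10.9 + 6.5 = 17.4 of 51.1, a loss of 66%. Power (unpooled): standard error √(0.224×0.776/48.5 + 0.109×0.891/59.7) = 0.072; 0.1156/0.0722 − 1.96 = −0.36; power 36%.

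**Range over assumed timing.** The power range covers unpooled and pooled two-proportion tests and the Schoenfeld formula.

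| k | Converters dropped | Events left | Power |
|---|---|---|---|
| 0.7 (early conversions) | 75% | 12.7 | 27–29% |
| 1 | 66% | 17.4 | 36–38% |
| 1.5 | 53% | 24.1 | 48–49% |
| 2 (late conversions) | 42% | 29.6 | 56–58% |

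**Other readings of assumption (ii).** If any conversion before the year 5 visit ends participation, nearly 100% of converters are dropped. If all converters continue to year 5, conversion itself drops 0%. In that case, at the planned 5% drop-out, 71×0.95 = 67.45 per arm remain and power is about 78%. The selection problem stays but cannot be sized from the document.

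**What the scenario does not show.** The planned rates imply a hazard ratio of ln 0.75 / ln 0.53 = 0.453. Among the remaining patients at k = 1 it is ln(1−0.109)/ln(1−0.224), again 0.453. Under exact proportional hazards and with no other selective loss, these calculations show lost events and understated rates, not a shifted hazard ratio.

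**The case against.** The strongest reply is that the text never says converters are removed. *Three courses* is undefined, and treatment is continuous over 5 years. Conversion is listed as an endpoint criterion beside finishing treatment, so a converter might be regarded as having completed. Progression leads to withdrawal only where stopping is judged necessary, which implies that some patients with progression continue. The completer sentence also closes a list of withdrawal reasons and may be meant only for patients who withdrew.

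Much of this stands. A reader might infer that the rule, as written, removes most converters; the document does not support that as a flat statement. It does make early exit likely for many. A patient who develops motor signs newly meets an exclusion criterion, which is a listed reason for withdrawal, and nothing exempts converters from the completer rule. Conversion without such signs would not be caught by that item, so the share cannot be fixed.

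A reader might also count the safety population as a third conflicting rule, since it "should contain all the participants that have been administrated with the experimental drug". That does not hold: a safety set is defined for a different purpose and is compatible with either efficacy set.

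None of this removes the contradiction. Even if the sentence covers only withdrawn patients, excluding them from the final analysis is not intention-to-treat.

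**Conclusion.** The contradiction between the completer rule and the intention-to-treat statement is certain and needs correcting. It does not depend on any assumption about converters, and it is not a detail left to an analysis plan: the article fixes two incompatible rules for the same analysis.

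The loss of primary events is conditional. It requires that the three courses are the year 1, 3 and 5 evaluations and that converters leave, which the text suggests but does not state. On those terms the loss is 66% of converters under constant hazards, with power about 36%, and 42% to 75% over the timings tried, with power from about 58% down to 27%. The extremes are no loss through conversion if all converters continue, and almost complete loss if any conversion before year 5 ends participation.

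**What to change.** 1. Delete the completer sentence from the withdrawal criteria, or relabel it as a completers sensitivity analysis and define *course*.
2. State that the primary analysis includes all randomised patients in their assigned arm, and that a conversion counts as an event at whichever assessment it is found.
3. State that patients who stop treatment stay in the analysis with whatever conversion assessments are available, and are censored at the last one only if none follow.
4. State that a withdrawal for disease progression that meets the diagnostic criteria is a conversion and not a censored observation. Otherwise the censoring itself would be related to outcome.
5. Reconcile the endpoint, exclusion and withdrawal sections so that the reader can tell what happens to participation at conversion. Which clinical rule applies is for the investigators.

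The cost is a few sentences in the protocol, repeated in the analysis plan where it covers the same ground. No extra patients or procedures are needed. The change should be made before unblinding, so that the analysis set cannot be chosen with the results in view.

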### Recruitment, screening and baseline assessment

Patients from the three centers will be recruited successively from July 2020 to July 2021. The baseline information will be collected and physical examinations will be conducted to assess the eligibility of each patient. Baseline demographics include sex, age, education level, occupation, concomitant disease and medications, etc. Blood testing is required to detect the blood biomarkers (neuronal exosomal α-synuclein, SNCA methylation, inflammatory cytokines and chemokines), as well as liver and kidney function to exclude patients with contraindications. In addition, patients will undergo (^18^F-FP-CIT) dopamine transporter (DAT)-PET/ MRI neuroimaging examinations.

### Randomization and blinding procedures

A random-number table based on block randomization was prepared by an independent biostatistician. Patients will be randomized equally to idebenone or identical-looking placebo group. If eligible individuals are invited to participate in the study and provide written informed consent, the randomized code and treatment will be assigned in a sealed envelope. Assessors are specific in each center, and both investigators and patients will remain fully blinded to the allocation throughout the study.

### Intervention and follow-up

During the 5-year treatment, patients will undergo oral administration of idebenone or placebo with a dosage of 30 mg each time, three times a day. Given idebenone is prescribed conventionally for cerebral infarction, cerebral hemorrhage, and atherosclerosis sequelae caused by brain dysfunction, the optimal dosage is recommended by the instruction of idebenone (30 mg per tablet, Shenwei, Qilu Pharmaceuticals, China). We also deliberated the administration according to preliminary literatures and clinical trials in the use of neurodegenerative disorders (27–29). Therefore, the dosage is fixed without setting dose gradient as control groups. The drug will be kept by blinded nurses, and distributed to patients according to the code. Routine blood testing and liver function will be monitored every 6 months during the administration. Once serious side effects occur, such as leukopenia, liver function damage or severe allergic reaction, participants should discontinue or withdraw from the trial. The follow-up evaluations of patients include the assessment of rating scales, blood testing and neuroimaging examinations. Movement Disorder Society-Unified Parkinson's Disease Rating Scale (MDS-UPDRS), Mini-Mental State Examination (MMSE), Montreal Cognitive Assessment (MoCA), Sniffin' Sticks test-16 (SS-16), 17-Item Hamilton Rating Scale for Depression (HAMD-17), Non-Motor Symptom Questionnaire (NMSQ) and Scales for Outcomes in Parkinson's Disease-Autonomic questionnaire (SCOPA-AUT) is used to quantify the progression of motor and non-motor symptoms. In view of the favorable improvement on neurodegenerative disease of idebenone, it is speculated that idebenone might ameliorate RBD symptoms as well (30). Therefore, we use REM sleep behavior disorder screening questionnaire (RBDSQ) to identify the influence. Plasma exosome-synuclein levels will be tested to provide convictive biomarkers for neurodegeneration. Several inflammatory cytokines and chemokines (interleukin-6 (IL-6), IL-8, IL-10, tumor necrosis factor-α (TNF-α), TGF-β, C-X-C motif ligand (CXCL) 12, C-X3-C motif ligand 1 (CX3CL1), C-C motif ligand (CCL) 3, CCL15 and CCL20) will be measured based on our previous investigation (31). The SNCA methylation will also be analyzed by bisulfite sequencing (32, 33). In addition, according to our previous publications, functional connectivity impairment and increased free water in the posterior substantia nigra are indicative imaging markers for phenoconversion (34–36). PET/MRI can also provide supplementary evidence for dopaminergic neurodegeneration, which is necessary for the participants in the follow-up evaluation.

### Outcome measures

The primary outcome is the comparison of conversion rate from iRBD to synucleinopathies between idebenone and placebo group, measured at 5-year of follow-up. Clinical symptoms will be evaluated by physicians using comprehensive rating scales. PET/MRI will be carried out to reflect the dopaminergic degeneration. The secondary outcome is the safety and tolerability of idebenone in the treatment of patients with iRBD. The objects for safety evaluation should contain all the participants that have been administrated with the experimental drug. Safety evaluation including the laboratory test results, the events of death and adverse reactions, will be recorded in detail and analyzed after the trial (Table 1).

**Table 1 T1:** Outcome measures taken at baseline and follow-up.

**Endpoint**		**Measure**	**Evaluating methods/criterion**	**Time points**
Primary	Effectiveness: 5-year conversion rate of iRBD into synucleinopathies	Rating scales	MDS-UPDRS, RBDSQ, MMSE, MoCA, SS-16, HAMD-17, NMSQ, SCOPA-AUT	Baseline, 1, 3, 5 years
		Blood testing	Biomarkers including neuronal exosomal α-synuclein, SNCA methylation, inflammatory cytokines and chemokines (IL-8, TNF-α, TGF-β, IL-10, IL-6, CXCL12, CX3CL1, CCL15, CCL3 and CCL20)	
		Neuroimaging examinations	(^18^F-FP-CIT) DAT-PET/ MRI	
Secondary	Safety and tolerability	Vital signs	Body temperature > 39.5°C, pulse rate <50 beats/min, blood pressure < 80/60 mmHg, blood pressure > 220/120 mmHg, oxygen saturation < 90%;	Every 6 months
		Electrocardiogram	Atrial fibrillation, complete atrioventricular block, sinus arrest, ventricular tachycardia, ventricular fibrillation, pathologic Q-waves, arched ST-segment elevation	
		Laboratory tests	The ratio of alanine aminotransferase to aspartate aminotransferase over twice the normal values after treatment, the creatinine over twice the normal value, glomerular filtration rate lower than 20 ml/min, red blood cell, hemoglobin, white blood cell and platelet count <50% of the lower normal limit or more than twice the upper normal limit	
		Adverse events	Result in death, are immediately life-threatening or cause severe organ damage	

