### Study designs

EITRS is a randomized, double-blind, multi-center clinical study with two parallel arms in 1:1 ratio to evaluate the efficacy and safety of idebenone in patients with iRBD compared with placebo. The total study duration of 6 years comprises a 1-year enrollment period and a 5-year intervention period. One hundred forty-two eligible participants will be allocated to idebenone or placebo group randomly and equally after baseline assessment. Follow-up evaluations will be conducted at the 1st, 3rd and 5th years of treatment in any of the three centers to detect the disease progression. Routine blood testing and liver function will be monitored every 6 months during the administration. Participants, investigators and statisticians are masked to the allocation code. The flowchart of the trial is outlined in Figure 1. The EITRS study is registered with ClinicalTrial.gov (Register Number: NCT 04534023).

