### Discontinue criteria of intervention

Severe liver and kidney function abnormality associated with the intervention (transaminase increase more than twice of the normal value);Severe blood testing abnormality: red blood cell, hemoglobin, white blood cell or platelet count <50% of the lower normal limit, or more than twice the upper normal limit;Severe allergic reactions or arrhythmias: severe hypertension (blood pressure > 220/120 mmHg) or hypotension (blood pressure < 80/60 mmHg) caused by intervention; or severe arrhythmias (heart rate < 50 beats/min, heart rate > 140 beats/min or atrial fibrillation) and sinus arrest; or respiratory disorder (oxygen saturation < 85%);Consciousness disorders: coma, delirium or convulsions.

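### Table 1 words the liver criterion of the safety endpoint as an ALT-to-AST ratio, which does not measure how far either enzyme has risen

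*Protocol article*

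**What the plan says.** The article has one secondary endpoint, safety and tolerability (Abstract, Study aims, Outcome measures). The Laboratory tests cell for that endpoint in Table 1 opens with the liver criterion: "The ratio of alanine aminotransferase to aspartate aminotransferase over twice the normal values after treatment". It is the only numeric liver threshold in the table. The cell continues with renal criteria: "the creatinine over twice the normal value, glomerular filtration rate lower than 20 ml/min". It then sets blood-count limits against the lower and upper normal limits.

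Liver enzymes have a numeric threshold in one other place, the first item under Discontinue criteria of intervention: "transaminase increase more than twice of the normal value". That is a stopping rule, not a second definition of the endpoint.

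On use of the data, Outcome measures says: "Safety evaluation including the laboratory test results, the events of death and adverse reactions, will be recorded in detail and analyzed after the trial". On monitoring, Study designs says: "Routine blood testing and liver function will be monitored every 6 months during the administration".

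**The concern.** A criterion for liver abnormality should respond to how far an enzyme has risen. The quotient of two enzymes does not. It reflects which one dominates, so large rises in both can leave it at its usual value and a low AST can push it up with nothing raised. The cell also gives no normal ratio, so anyone applying it as printed would have to supply one.

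At stake is the classification of liver abnormalities in the only secondary endpoint. The article itself treats liver injury as a foreseeable harm (Intervention and follow-up): "Once serious side effects occur, such as leukopenia, liver function damage or severe allergic reaction, participants should discontinue or withdraw from the trial". If the cell were applied literally, a comparison of liver abnormalities between arms would leave out real elevations, could include normal results, and would not agree with the stopping rule.

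**Working it through.** This is a definition, so there is no stated figure to reproduce. The check compares the printed rule with a level rule on example enzyme values.

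**Inputs**
- Printed rule: ALT/AST above twice normal (Table 1, Laboratory tests).
- Level rule: a transaminase above twice normal (Discontinue criteria of intervention), applied to either enzyme.
- Not in the article, so assumed: the normal ratio. I also read the normal value of an enzyme as its upper limit.

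**Formulas.** Let *a* and *s* be ALT and AST, each as a multiple of its own normal value. Let *k* be the normal ratio staff would apply, divided by the ratio of the two normal values.
- The printed rule flags if *a*/*s* > 2*k*. I took *k* from 0.75 to 1.5, so the cut-off runs from 2 × 0.75 = 1.5 to 2 × 1.5 = 3.0. It is 2.0 when *k* = 1.
- The level rule flags if *a* > 2 or *s* > 2.

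**Two results in general form**
- Proportional rise, *a* = *s* = *m*: *a*/*s* = 1 for every *m*. A flag needs 1 > 2*k*, that is *k* < 0.5, which is outside the range.
- AST-dominant rise, *s* > *a*: *a*/*s* < 1, so the ratio moves away from the cut-off.

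**Examples**

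| ALT / AST (multiples of normal) | *a*/*s* | Level rule | Printed rule, cut-off 1.5 to 3.0 |
|---|---|---|---|
| 2.1 / 2.1 | 1.00 | flagged | missed throughout |
| 5 / 5 | 1.00 | flagged | missed throughout |
| 10 / 10 | 1.00 | flagged | missed throughout |
| 2 / 5 | 0.40 | flagged | missed throughout |
| 1 / 3 | 0.33 | flagged | missed throughout |
| 3 / 2 | 1.50 | flagged | missed throughout |
| 2.5 / 1.5 | 1.67 | flagged | flagged only if cut-off is below 1.67 |
| 5 / 2 | 2.50 | flagged | flagged only if cut-off is below 2.5 |
| 0.9 / 0.4 | 2.25 | not flagged | flagged if cut-off is below 2.25 |
| 0.9 / 0.25 | 3.60 | not flagged | flagged throughout |

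**Second check in enzyme units.** Assume an upper limit of 40 U/L for both enzymes, so the level rule is > 80 U/L, and normal ratios of 1.0, 1.25 and 1.5, so the cut-offs are 2.0, 2.5 and 3.0.
- ALT/AST 200/200 (ratio 1.0), 60/300 (0.2) and 120/80 (1.5) are missed at all three cut-offs. The level rule flags all three.
- 38/12 (3.17) is flagged at all three, and 38/15 (2.53) at 2.0 and 2.5 only. Both enzymes are normal in both pairs, and the level rule flags neither.
- 300/90 (3.33) is flagged by both rules at every cut-off. The two agree when ALT dominates strongly.

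**Was a level meant?** Three features of the text point that way.
- The next item in the cell is a level with the same multiple: "the creatinine over twice the normal value".
- The stopping rule applies that multiple to the transaminase level.
- The enzyme item refers to normal values in the plural and the creatinine item to a single normal value. The plural suits two enzymes, each with its own limit, better than one ratio.

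No section gives a reason for using a ratio.

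**The case against.** The strongest reply is that this is a slip of wording in a condensed article, that a reader can recover the intended rule from it, and that staff would work from the full protocol and case report form, which are not shown. Since the cell gives no normal ratio, it cannot be applied literally without inventing one, and the natural fallback is the enzyme level in the stopping rule.

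There are other safeguards too. Under Serious adverse event and adverse event reporting, liver and kidney function are recorded at baseline and later results are compared with baseline. Adverse events are defined broadly enough to capture a rise in either enzyme. The Adverse events row of Table 1 brings severe organ damage into the same endpoint. Finally, the enzyme pairs are hypothetical, and the pair flagged throughout needs an AST at a quarter of its upper limit.

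Most of this stands as a limit on the harm. It does not make the criterion right. The stopping rule covers only abnormality attributed to the intervention and governs treatment. The safety evaluation covers everyone given the study drug, and the cell requires no judgement of causality. Baseline comparison and adverse event recording do not supply a correct threshold for classifying laboratory results. The results for proportional and AST-dominant rises do not depend on which pairs are chosen, provided the cut-off lies in the assumed range.

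**Conclusion.** The concern holds as a minor error of wording. As printed, the only numeric liver threshold of the sole secondary endpoint misses proportional and AST-dominant rises of any size at every cut-off from 1.5 to 3.0. It can also flag results in which both enzymes are normal. Strongly ALT-dominant rises can still be caught, depending on the cut-off.

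The cut-off range is an assumption, because the article gives no normal ratio. That the cell was meant to say ALT or AST is an inference, though a well-supported one. How many participants would be misclassified cannot be derived from the article. The primary endpoint, the sample size, the 6-monthly liver tests and the level-based stopping rule are unaffected.

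**What to change.** In the Laboratory tests cell of Table 1, replace the ratio with: *ALT or AST level over twice the upper normal limit*. This restores a level, in line with the creatinine item and the stopping rule. Naming the upper limit goes slightly further than those two, which refer only to a normal value, but the blood-count item in the same cell already uses that reference point, and it removes an ambiguity.

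The cost is the wording of one cell. Liver function is already tested every 6 months, so no new tests or data are needed. The wording should be settled before the safety data are analysed, while the allocation is still masked.
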